**Methods/Design:**

The STAR trial is an NIHR HTA-funded UK pragmatic randomised phase II/III clinical trial in the first-line treatment of advanced RCC. Participants will be randomised (1:1) to either a sunitinib CCS or a DFIS. The overall aim of the trial is to determine whether a DFIS is non-inferior, in terms of 2-year overall survival (OS) and quality adjusted life years (QALY) (averaged over treatment and follow up), compared to a CCS. The QALY primary endpoint was selected to assess whether any detriment in terms of OS could be balanced with improvements in quality of life (QoL). This is a complex trial with a number of design challenges, and to address these issues a feasibility stage is incorporated into the trial design. Predetermined recruitment (stage A) and efficacy (stage B) intermediary endpoints must be met to allow continuation to the overall phase III trial (stage C). An integral qualitative patient preference and understanding study will occur alongside the feasibility stage to investigate patients’ feelings regarding participation or non-participation in the trial.

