## Background

### Renal cell carcinoma

Renal cell carcinoma (RCC) constitutes only 3% of adult malignancies, but is the sixth leading cause of cancer-related death due to the lack of effective therapy for locally advanced and metastatic disease.

The strategy of targeting angiogenic pathways has produced positive results in advanced RCC. Tyrosine kinase inhibitors (TKIs), e.g. sunitinib and sorafenib, and monoclonal antibodies, e.g. bevacizumab with IFNα, have produced improvements in terms of progression free survival (PFS) and overall survival (OS). Sunitinib (Sutent™) selectively targets multiple protein receptor tyrosine kinases including vascular endothelial growth factor receptor and platelet-derived growth factor receptor. This inhibits tumoural delivery of blood and nutrients required for growth, which ultimately leads to cancer cell death. Sunitinib also has a direct inhibitory effect on tumour cells
[1].

The landmark sunitinib trial in RCC was a double-blind randomised controlled trial of 750 patients (ECOG performance status 0 or 1) with metastatic RCC which compared sunitinib to IFNα as first-line therapy
[2]. The primary endpoint was PFS and the trial was unblinded after a second interim analysis demonstrated significant benefit in patients treated with sunitinib. Updated results were published in 2009 and demonstrated a median PFS of 11 months with sunitinib and 5 months with IFNα in the intention-to-treat population (p<0.001)
[3]. The OS was 26.4 months with sunitinib and 21.8 months with IFNα (HR 0.821; 95% confidence intervals [CI]=0.673-1.001, p=0.051), however this difference is likely to be an underestimate due to significant crossover from IFNα to sunitinib after unblinding. Sunitinib was also associated with improved response rates over IFNα (47% vs 12%).

Sunitinib was approved by NICE in 2009 for UK use in the first-line treatment of advanced RCC in patients with a good performance status (ECOG 0 or 1) until evidence of disease progression or unacceptable toxicity
[4]. This was after reappraisal under the specific ‘end-of-life’ criteria as it had not previously been approved under standard NICE decision-making criteria.

Sunitinib is associated with a significant side effect burden. The landmark first-line trial reported that 19% of patients discontinued sunitinib due to adverse events (AEs) and 50% of patients required a dose reduction

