### Statistical methods and analysis

Statistical analysis will be the responsibility of the STAR CTRU Trial Statistician. A full statistical analysis plan will be written before any formal analyses are undertaken.

All non-inferiority analyses will be conducted on both the ITT and per protocol analysis populations. For the superiority endpoints the ITT analysis will be given primacy, however for the non-inferiority endpoints equal weighting will be given to both the ITT analysis and the per-protocol analysis, as the ITT is likely to be the least conservative approach when testing for non-inferiority. An overall two-sided 5% significance level will be used for all superiority endpoint comparisons, and a one-sided 2.5% significance level will be used for all non-inferiority endpoints.

A formal interim analysis will take place after stages A and B (at 21 months after the start of recruitment). A feasibility and efficacy stopping rule have been specified (as detailed below) to ensure the trial is stopped as early as possible in the case of insufficient recruitment (Stage A) or insufficient efficacy (Stage B) in the DFIS arm. The DMEC in light of this interim data will make their recommendations to the Trial Steering Committee who will in turn decide whether the trial can continue to Stage C.

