#### Stage B

An interim efficacy endpoint has been included to further ensure the appropriateness of extending recruitment and continuing the trial to stage C. PFS is not an appropriate comparator endpoint in the trial as, due to planned treatment breaks, the initial PFS is likely to be shorter in the DFIS arm compared to the CCS arm. TSF will be analysed (targeted to look at differences in 15 months strategy failure rates) in both arms and non-inferiority will be required to be demonstrated between the arms for the trial to continue to stage C. The TSF in the DFIS arm must be less than 15% worse than in the CCS arm (strategy failure assumed to be 80% at 15 months). Assuming 21 months of accrual and immediate analysis, 80% power, and assuming proportional hazards, this would require 67 events and a population of 112 patients (56 in each arm; approximately 53% of the 210 in total that will be randomised) who take up their randomisation at 6 months.

During the formal interim analysis, an analysis of the utility data so far obtained will also be performed to revise the estimates of the power to detect the composite QALY endpoint and to evaluate possible refinements in the trial design as a result.

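### Stage B's unsourced 80% strategy failure at 15 months sits poorly with the protocol's own 11-month median PFS on sunitinib, and the 15-point margin has no fixed meaning on the hazard-ratio scale of the Cox model

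*Protocol article*

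**What the plan says.** Under Statistical methods and analysis, Stage B, the protocol article makes continuation to Stage C conditional on showing non-inferiority for TSF. The margin is "The TSF in the DFIS arm must be less than 15% worse than in the CCS arm", with "strategy failure assumed to be 80% at 15 months". The sizing statement reads "Assuming 21 months of accrual and immediate analysis, 80% power, and assuming proportional hazards", and "this would require 67 events and a population of 112 patients". The 112 are those who take up their allocated strategy at 6 months, given as "approximately 53% of the 210 in total that will be randomised". No source is given for the 80%, and no hazard ratio is stated for this margin.

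The general statistical section says that "a one-sided 2.5% significance level will be used for all non-inferiority endpoints". The Stage C text, which also covers the Stage B analysis, plans Kaplan-Meier curves with a confidence interval for the difference, but gives primacy to the Cox model.

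The Background (Renal cell carcinoma) reports that the first-line registration trial, in patients of ECOG performance status 0 or 1, "demonstrated a median PFS of 11 months with sunitinib and 5 months with IFNα in the intention-to-treat population".

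**The concern.** The CCS arm is sunitinib continued until progression or intolerable toxicity, with no planned breaks, in patients of the same performance status as the cited trial. By the definition in the Endnotes, its TSF events are mainly progression on sunitinib and death, which are PFS events. Stopping for toxicity alone is not an event. The protocol sets PFS aside because of the breaks in the drug-free interval (DFIS) arm, which is no reason to expect CCS patients to fail much earlier than the cited PFS.

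If the base rate is wrong, an absolute margin of 15 points and a hazard-ratio margin derived from it at 80% part company. Either the Cox test tolerates a larger absolute loss than 15 points, or the 15 points are kept and the stated events do not give the stated power. This test decides whether a further 790 patients are recruited.

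**Working it through.** **Inputs.** From Stage B: 80% failed at 15 months, a 15-point margin, 21 months of accrual with immediate analysis, 67 events, 112 of 210 patients. From the general statistical section: one-sided 2.5%. Allocation is 1:1. From the Background: median PFS 11 months. Assumed here: exponential times and uniform accrual. Hazard ratios are DFIS over CCS.

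**1. Reproducing the plan.**
- Hazard h = ln(5)/15 = 0.1073 per month; median ln(2)/h = 6.46 months.
- Failure-free at 6 months: exp(-6h) = 52.5%, against the stated 53%.
- Event probability over 21 months: 1 - (1 - exp(-21h))/(21h) = 0.603; 112 × 0.603 = 67.5 events, against the stated 67.
- Margin: 20% vs 5% failure-free gives HR = ln(0.05)/ln(0.20) = 1.861.
- Events for 80% power, Schoenfeld / Freedman: 65 / 69 at one-sided 5%, but 82 / 87 at one-sided 2.5%. So 67 fits one-sided 5%. At 2.5%, power is Φ(ln(1.861) × √67/2 - 1.96) = 72%.

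Stage B is thus consistent with an exponential curve at 80% in the control arm. The one-sided 5% behind the 67 events is a separate problem.

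**2. The cited trial.**
- Failed at 15 months: 1 - 0.5^(15/11) = 61.1%.
- Failure-free at 6 months: 0.5^(6/11) = 68.5%, not 53%.
- Hazard needed for 80%, relative to the cited PFS: 0.1073/(ln(2)/11) = 1.7 times.
- For comparison, Stage C agrees with this same trial. Its median OS of 26.4 months gives 0.5^(24/26.4) = 53.3% at 2 years, and ln(0.5325)/ln(0.4575) = 0.806, the stated Stage C hazard ratio.

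**3. The margin at an 11-month median.**
- 15 points: 38.9% vs 23.9% failure-free, HR = ln(0.2386)/ln(0.3886) = 1.516.
- HR 1.861 instead: 0.3886^1.861 = 17.2% failure-free, a deficit of 21.6 points.

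**4. Power for 15 points at an 11-month median, one-sided 2.5%**, Φ(ln(1.516) × √events/2 - 1.96). The event probability over 21 months is 0.4455.

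| Events | Origin | Power |
|---|---|---|
| 50 | 112 × 0.4455 | 31% |
| 67 | as stated | 40% |
| 94 | 210 × 0.4455 | 52% |

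About 182 events (Schoenfeld) would be needed for 80%.

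**5. Sensitivity to the CCS median.**

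| Median (months) | Failed at 15 months | HR equal to 15 points | Points tolerated by HR 1.861 |
|---|---|---|---|
| 6.46 (plan) | 80% | 1.86 | 15.0 |
| 8 | 73% | 1.61 | 18.4 |
| 9 | 69% | 1.56 | 19.9 |
| 11 | 61% | 1.52 | 21.6 |
| 12 | 58% | 1.51 | 22.1 |

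**The case against.** TSF is not PFS. It adds the start of a new systemic agent and clinical deterioration without imaging, and 19% of patients in the cited trial stopped sunitinib for adverse events, some of whom could go on to another agent. STAR is also pragmatic and includes poor-risk patients. This stands in part. It makes 61% closer to a floor than a replacement value, so a reader should not infer that the documents show 61% to be the right figure. It does not establish 80% either. Adding all 19% to 61% would just reach 80%, but only if every one of those patients were otherwise progression-free at 15 months and had started a new agent. The protocol makes no such argument.

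HR 1.86 appears nowhere in the protocol. A reader might infer that the trial will pass a strategy about 22 points worse. That follows only if a hazard ratio derived at 80% is carried into the Cox test whatever the control rate, and the analysis plan may define it otherwise. The absolute difference is also already to be estimated by Kaplan-Meier. What stands is that the Cox model has primacy while the margin is given only in points.

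A reader might also put the whole fall from 80% to 40% power down to the base rate. The documents do not support that: 67 events give 72% at one-sided 2.5% even at 80% vs 95%. Nor is 67 a natural event count at a slower failure rate. The count would be about 50 or 94, depending on whether 112 or all 210 patients are analysed, and the protocol gives the ITT and per-protocol analyses equal weight.

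Finally, a mistaken decision to continue leaves the Stage C tests and committee review in place. That limits the harm but does not repair the gate.

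**Conclusion.** The concern holds as an unsupported base rate and a margin not tied to one scale. The 80% is unsourced and needs about 1.7 times the hazard implied by the protocol's cited PFS. The 15-point margin corresponds to an HR of 1.86 only at that rate. Over CCS medians of 8 to 12 months (73% to 58% failed) it corresponds to about 1.61 to 1.51. At an 11-month median, power for 15 points lies between about 31% and 52%, depending on the events available, against a like-for-like 72% for 67 events on the plan's own rates.

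These figures rest on exponential times (the protocol states only proportional hazards, though 67 of 112 fits an exponential), on reading the 80% as the CCS rate (the event arithmetic supports this, the text does not say it), and on PFS as an approximate lower bound for CCS failure. The conflict is with the cited trial. Stage B's uptake and event fraction agree with its own 80%. The point should be settled before the Stage B interim analysis because it governs the decision to continue.

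**What to change.** In the Stage B section:

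1. Give the basis for 80% failure at 15 months, or replace it with a rate consistent with the cited 11-month median, with a sensitivity range such as CCS medians of 8 to 12 months.
2. State the margin on one scale. Either make the already planned Kaplan-Meier difference at 15 months the decision test, or state the hazard ratio that equals 15 points at the revised rate (about 1.5 at 61%) and use it in the Cox model.
3. Restate the 6-month uptake (about 69% at an 11-month median), the expected events in the take-up and full randomised populations, and the Stage B power at one-sided 2.5%.

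The cost is protocol wording and a recalculation, with no new data and no added enrolment. The drawback is real: the stated power becomes clearly less favourable, so the gate may stop a truly non-inferior strategy more often than the present text suggests. The oversight committees should know this before they apply it.

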### Endnotes

^a^TSF is defined as the time from randomisation until death; disease progression on sunitinib; disease progression in the DFIS arm during a planned treatment break assuming no further disease response or stabilisation on subsequent sunitinib occurs; participant requires use of a new systemic anti-cancer agent for RCC or significant clinical deterioration where deterioration is assumed to be due to renal cancer progression and not another comorbidity and deterioration sufficient to warrant cessation of sunitinib if on treatment or to preclude restarting sunitinib if on a treatment break on the DFIS arm, without it being clinicially appropriate to arrange radiological confirmation of the progression

^b^SPFI is defined as the sum of the intervals from the start of each treatment block with sunitinib, until radiological evidence of disease progression provided there has been some evidence of disease control prior to ongoing progression

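### The Stage B analysis at month 21 cannot contain the 67 events in 112 strategy-takers on which its 80% power rests; about 30-40 events (40-52 on a second reading) and 39-50% power (up to 61%) are expected.

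*Protocol article*

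**What the plan says.** Under Stage B, the protocol article requires non-inferiority on time to strategy failure (TSF) before the trial may enter Stage C. The margin is "The TSF in the DFIS arm must be less than 15% worse than in the CCS arm", with "strategy failure assumed to be 80% at 15 months". The size is set as follows: "Assuming 21 months of accrual and immediate analysis, 80% power, and assuming proportional hazards", "this would require 67 events and a population of 112 patients". The 112 are described as "approximately 53% of the 210 in total that will be randomised) who take up their randomisation at 6 months".

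Three other places bear on this:

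- Statistical methods and analysis: "A formal interim analysis will take place after stages A and B (at 21 months after the start of recruitment" (Data collection and management gives the same month), and "a one-sided 2.5% significance level will be used for all non-inferiority endpoints".
- Recruitment and Intervention: stages A/B recruit over the same 21 months, and the strategy is taken up only after at least four 42-day cycles and maximal response.
- Endnotes: "TSF is defined as the time from randomisation until death" or another listed failure event.

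**The concern.** The powered population consists of people who have reached six months. With recruitment and analysis both ending at month 21, anyone randomised in the last six months is not yet a taker. Those who are takers have 0-15 months on their allocated strategy, not 0-21. The number of patients, the number of events, the analysis date and the power are all stated, and they cannot all hold.

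The test decides whether a 1000-patient trial goes on. If it holds far fewer events than planned, a drug-free interval strategy that is truly as good as continuation may fail the requirement for lack of data.

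**Working it through.** **Inputs.** 80% failed at 15 months, 15-point margin, 112 of 210 taking up at 6 months (Stage B); one-sided 2.5% and analysis at month 21 (Statistical methods and analysis); 210 patients in 21 months (Sample size, Recruitment); 13 per month in months 10-21, or at least 133 in that period (Stage A).

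**Reproducing the plan.**

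- Exponential hazard: λ = ln(5)/15 = 0.1073 per month.
- Failure-free at 6 months: exp(-6λ) = 0.525, matching the stated 53% (112/210 = 0.533).
- Margin of 80% against 95% failed: HR = ln(0.05)/ln(0.20) = 1.861, ln HR = 0.6213.
- Uniform entry over 21 months with immediate analysis: P(event) = 1 - (1 - exp(-21λ))/(21λ) = 0.603. Then 112 × 0.603 = 67.5, the plan's 67.
- Events for 80% power, 4(z_α + 0.842)²/0.6213²: 65 at one-sided 5% (69 by Freedman's formula), 82 at one-sided 2.5% (87 by Freedman).

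So 67 of 112 treats takers as if they entered throughout the 21 months and were followed from entry, and 67 fits 80% power only at one-sided 5%.

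**Takers and events at month 21.** A person randomised at month t ≤ 15 has 15 - t months after take-up.

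- Takers = 0.525 × number randomised by month 15.
- Events = 0.525 × Σ rate × ∫(1 - exp(-λu))du over the available post-take-up time u. The integral is 1.576 over 0-6 months and 5.968 over 6-15 months, 7.544 in total.
- Power with truly equal arms = Φ(0.6213√d/2 - 1.96), where d is the number of events.

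| Recruitment | Randomised by month 15 | Takers | Events | Power, 2.5% | Power, 5% |
|---|---|---|---|---|---|
| Uniform, 10 per month | 150 | 79 | 10 × 0.525 × 7.544 = 39.6 | 50% | 62% |
| 77 in months 1-9, then 133 | 143.5 | 75 | 0.525 × (8.56 × 5.968 + 11.08 × 1.576) = 36.0 | 46% | 59% |
| 54 in months 1-9, then 156 | 132 | 69 | 0.525 × (6 × 5.968 + 13 × 1.576) = 29.6 | 39% | 52% |

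Using 0.533 in place of 0.525 raises takers to 70-80 and events to 30.0-40.2.

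**Second reading.** If 80% failure at month 15 applies to takers only, their hazard after month 6 is ln(5)/9 = 0.179. Events become 40-52 and power at 2.5% becomes 50-61%.

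**Separating the two causes.** With 67 events, power at one-sided 2.5% is Φ(0.6213 × 8.185/2 - 1.96) = Φ(0.58) = 72%. The significance level accounts for 80% to 72%; timing accounts for 72% to 39-50%. At one-sided 5%, timing alone takes about 81% to 52-62%.

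**When the events arrive.** With recruitment continuing at 10-13 per month, 67 post-take-up failures are expected at about month 27-28.5 and 82 at about month 30-31.

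**All randomised patients.** From randomisation, 113 (54 then 156) to 127 (uniform) failures are expected by month 21, giving nominal power of 91-94% at 2.5% if the true HR is 1. Of these, 112.7 - 29.6 = 83.1 (74%) and 126.6 - 39.6 = 87.0 (69%) fall in the first six months, when both arms are treated alike.

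**The case against.** The strongest reply is that TSF runs from randomisation and that the plan gives the intention-to-treat and per-protocol analyses equal weight, so the month-21 test is not confined to takers. This stands in part: it would be wrong to infer that only 30-40 strategy failures can exist at month 21. But about 70% of the intention-to-treat events precede any difference between the arms. That analysis is diluted, and it is not the calculation the plan presents.

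A reader might then infer that the diluted test would usually pass a strategy lying at the margin. The documents do not support that. An HR of 1.861 acting only after month 6 gives 1 - 0.525 × exp(-9 × 0.1073 × 1.861) = 91.3% failed at 15 months. That is 11.3 points worse, inside the 15-point margin on the stated clock. A full 15-point deficit needs a post-divergence HR of about 2.44.

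A reader might also infer that the trial would more likely than not be stopped. Only part of the power range lies below 50%, and only for the taker population. The monitoring committee recommends and the steering committee decides, although Trial design and Stage B use mandatory wording. Nor does the small number of people with a full 15 months of follow-up decide the matter, because the Cox model has primacy and uses censored times.

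Finally, takers are a subset formed after open-label randomisation, so restarting the clock at take-up would contradict the TSF definition and weaken the protection of randomisation. That objection stands, and the fix respects it.

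**Conclusion.** The point holds for the population on which the plan based its calculation. Month 21 offers roughly 60-70% of the intended takers and about half the intended events, or 60-78% of them (40-52 of 67) on the second reading. Power at the declared level is about half the stated 80%, and at best about 61%. It would be wrong to blame timing for the whole shortfall, since the mismatch of significance level removes the first eight points.

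The figures are expectations. They rest on a constant hazard, which the matches at 0.525 and 0.603 suggest is the plan's own model; on take-up at six months; and on recruitment of 210 in one of the three patterns shown. No pattern or reading examined brings the takers to 67 events or 80% power at month 21.

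**What to change.** Reconcile the analysis date in Statistical methods and analysis and in Data collection and management with the Stage B population and event count. There are two ways:

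1. Keep month 21 for the Stage A recruitment rule, and trigger the Stage B efficacy analysis when the required number of post-take-up strategy failures is reached. Set that number at about 82 if 80% power at one-sided 2.5% is intended; 67 gives 72%.
2. Keep month 21, restate Stage B power for the taker population as about 40-50%, and make the rule advisory to the monitoring committee.

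Under either, keep TSF measured from randomisation as defined, and state the significance level behind the event count.

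Both need a protocol amendment. The first delays the efficacy decision by about 6-10 months. At 10-13 recruits per month, that is roughly 60 (6 × 10) to 130 (10 × 13) more people randomised before any efficacy stop, against the plan's aim of stopping as early as possible. The second costs only a less favourable stated power and a weaker rule.

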#### Stage C

There are two co-primary outcome measures: OS and averaged QALY. The two null hypotheses are that DFIS is not inferior to CCS in terms of OS and QALYs. To calculate a sample size for the primary OS endpoint, a difference of ≤7.5% in OS at two years between the two arms has been assumed to be an acceptable non-inferiority margin (equivalent to a hazard ratio of 0.806). To demonstrate this non-inferiority with 80% power will require the recruitment of approximately 1000 patients (allowing for 10% of patients being lost to follow-up). To calculate a sample size for the primary QALY endpoint a difference of ≤10% in mean QALYs between the two arms has been assumed to be an acceptable non-inferiority margin. While it is hoped that survival will be equivalent between the two arms, a slightly poorer survival in the DFIS arm would be acceptable if offset by a significant QoL gain in these patients, this will be captured through the QALY measure. With a hazard ratio of 0.9 in favour of CCS and 1000 patients recruited, simulations give a power of 84% to show non-inferiority in the QALY endpoint. Both non-inferiority sample sizes are calculated assuming a 1-sided 97.5% confidence interval, as described by Kay
[26], and assuming patients are recruited in total over 4.5 years, with a further follow-up of 2 years before evaluating the data.

For Stage B TSF and Stage C OS endpoints, the primary analysis will comprise Kaplan-Meier curves including those adjusted for the minimisation factors
[27], giving 95% CIs for the TSF and 2-year survival difference. A a Cox proportional hazards model analysis adjusting for minimisation factors and associated hazard ratios plus 95% CIs for the DFIS vs. CCS comparisons will be pesented, as appropriate for the non-inferiority analysis. The analysis of primacy is the Cox model.

For the QALY endpoint mean differences in QALYs, calculated via the EQ-5D, between the arms, with 95% confidence limits, will be calculated. Multivariate linear regression will be used to adjust for minimisation factors. If the data are not normally distributed, transformations to normality will be investigated. If no such transformations can be found we will analyse the difference between median QALYs and we will calculate confidence intervals for the differences between these medians as described by Campbell and Gardner
[28].

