### Trial design

This is a pragmatic UK, multi-centre two-arm, randomised (1:1) controlled, multi-stage, open-label phase II/III trial in patients with inoperable locally advanced or metastatic clear cell renal cell cancer to evaluate the use of a sunitinib DFIS compared to the sunitinib CCS (see Figure 1). It is a particularly appropriate trial in the UK due to the need to develop treatment strategies that will allow patients access to treatments, which are delivered in the most beneficial and cost-effective way in the NHS. There are design challenges relating to this trial and a multi-stage approach has been utilised to optimise the effectiveness of the design in terms of time and sample size. The trial must meet pre-determined intermediary endpoints in stages A and stage B for recruitment to continue into stage C. Achievement of stage-specific endpoints will be assessed by an independent data monitoring and ethics committee (DMEC). 

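### The Stage C OS power of 80% leaves out the mandatory Stage B gate; with the gate included, a truly equivalent DFIS passes both steps about 64–67% of the time

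*Protocol article*

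**What the plan says.** Under Stage C, the protocol article sets the OS non-inferiority margin at 7.5 percentage points at two years, given as equivalent to a hazard ratio of 0.806. It continues: "To demonstrate this non-inferiority with 80% power will require the recruitment of approximately 1000 patients", after a 10% allowance for loss. Under Sample size, the 1000 covers all three stages, split as 210 in Stages A/B and 790 in Stage C. For QALY, Stage C reports 84% power from simulations with 1000 patients and a hazard ratio of 0.9 in favour of CCS.

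On the gate, the Trial design section says: "The trial must meet pre-determined intermediary endpoints in stages A and stage B for recruitment to continue into stage C". The Stage B section says of TSF that "non-inferiority will be required to be demonstrated between the arms for the trial to continue to stage C". It plans that test with 80% power and 67 events, against a margin of 15 points on an assumed 80% strategy failure at 15 months. The Statistical methods and analysis section calls this a stopping rule, has the DMEC recommend and the Trial Steering Committee decide, and states that "a one-sided 2.5% significance level will be used for all non-inferiority endpoints".

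**The concern.** Two tests stand in sequence, and each is planned at 80%. The Stage C power describes only the second. On the plan's own Stage B power, one trial in five of a truly equivalent DFIS would stop at 210 patients and never run the OS test at its planned size. The article gives no other OS power, so nothing tells the reader how often the design as a whole would confirm an equivalent strategy. That probability matters to those who fund the trial and to those who apply the gate, because the loss consists of false stops of an acceptable strategy.

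**Working it through.** **Inputs from the article.** OS margin HR 0.806; one-sided 2.5%; power 80%; 10% loss; 1:1 allocation; timing "assuming patients are recruited in total over 4.5 years, with a further follow-up of 2 years before evaluating the data". Stage B: 80% power, 67 events, failure of 80% versus 95% at 15 months.

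**Assumed input.** Stage C does not state a control-arm OS. I use the landmark trial's median from the Background ("The OS was 26.4 months with sunitinib and 21.8 months with IFNα") with exponential survival. Two-year OS is then 0.5325. At the margin it is 0.5325^(1/0.806) = 0.458, a difference of 7.5 points, so the assumption fits the stated margin.

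**1. Reproduce the 1000.**
- Deaths = 4(1.960 + 0.842)² / (ln 0.806)² = 675.
- Probability of death by the analysis (54 months' accrual plus 24 months' follow-up): 0.715 in the control arm and 0.785 at the margin, mean 0.750.
- 675 / 0.750 = 900, and 900 / 0.9 = 1000.

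This matches the stated figure, with no room in it for the gate. With the control probability in both arms, 900 × 0.715 ≈ 644 deaths give 78.1% power, a minor difference.

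**2. Add the gate at its stated power.** Let p_B = 0.80 and p_C = 0.80, both under equal arms. With a bivariate normal for the two test statistics, P(both pass) is:

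| Correlation | P(both pass) |
|---|---|
| 0 | 0.80 × 0.80 = 0.640 |
| 0.1 | 0.648 |
| 0.2 | 0.657 |
| 0.3 | 0.666 |

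At any correlation the result is at most min(0.80, 0.80) = 0.80.

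**3. Is the correlation range plausible?** Shared information limits it to about √(67/675) = 0.32. A log-rank simulation used 112 Stage B patients analysed at 21 months, 900 evaluable patients at the end, and patient-level TSF–OS correlation from 0 to 0.95. It gave correlations between the statistics of 0.06 to 0.28 and joint probabilities of 0.64 to 0.66.

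**4. Check the gate's own 80%.** The margin hazard ratio is ln 0.20 / ln 0.05 = 0.537.
- One-sided 2.5%: 82 events are needed for 80% power. With 67, power = Φ(|ln 0.537| × √67 / 2 − 1.960) = Φ(0.58) = 72%.
- One-sided 5%: 65 events are needed, and 67 give 81.5%.

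The 67 events therefore fit a one-sided 5% test, not the general 2.5% level. With p_B = 0.72, P(both pass) is 0.576 at correlation 0 and 0.607 at 0.3.

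**5. Stage A.** At the planned 156 patients in 12 months (Poisson), reaching 133 has probability about 97%, a small further loss not included above.

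**The case against.** The strongest reply is that nothing is miscalculated. Stage C gives the power of the final test at its planned size and never calls it the overall chance of success. That stands: a reader who infers that the 80% or the 1000 is an arithmetic error would be wrong, since both reproduce.

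It can also be said that the article is open about conditionality. The stage objectives, Sample size and Recruitment sections all describe later recruitment as depending on continuation. Those remarks qualify who is recruited and where, however, and not the stated power. Nor is this only a detail left to a fuller document: the continuation rule, the gate's power and the final power are all printed, and together they imply an overall figure well below the one given.

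The Trial Steering Committee takes the decision, so the gate might be applied with discretion. That is fair as a condition on the result, but the text words the gate as required and does not describe it as non-binding.

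Two stronger readings go too far. First, a reader might infer that both Stage C powers are single-stage and multiply 0.80 by 0.84 to get an overall QALY power. The 84% comes from simulations, and the article does not say whether they include the gate. It is also computed at a hazard ratio of 0.9, whereas the gate's 80% reproduces (at one-sided 5%) under equal arms, so the product describes no single scenario. Second, a reader might infer that the gate ought to be loosened. That would let through more strategies that are truly at the Stage B margin. It is a design choice that the documents do not settle.

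**Conclusion.** The point holds for OS as an unstated loss of power. With the gate's stated 80%, the overall chance is 13 to 16 points below the 80% given; with the gate at one-sided 2.5%, it is about 19 to 22 points below. These figures assume that DFIS equals CCS on TSF as well as OS, that the gate is applied as written, and that the two statistics are correlated at no more than about 0.3. The ceiling of 80% does not depend on the correlation. No overall figure can be given for QALY from the article.

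**What to change.** In the Stage C section, label the 80% OS power as conditional on passing Stage B and add the overall figure. For example: if DFIS and CCS are equal on TSF and OS and the Stage B rule is applied as written, the probability of passing both Stage B and the OS test is about 64–67%, taking Stage B power as 80% and the correlation of the statistics as 0 to 0.3. State the significance level of the Stage B test alongside, because at one-sided 2.5% the figure becomes about 58–61%.

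For QALY, state whether the simulations behind the 84% include the Stage B gate. If they do not, rerun them with the gate under the same hazard ratio of 0.9 and report that result; a product of the two printed powers should not be used instead.

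The cost is one sentence, possibly one rerun of an existing simulation, and a less favourable stated power.
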